## Abstract

**Background:**

The prevalence of type 2 diabetes is rising internationally. Patients with diabetes have a higher risk of cardiovascular events accounting for substantial premature morbidity and mortality, and health care expenditure. Given healthcare workforce limitations, there is a need to improve interventions that promote positive self-management behaviours that enable patients to manage their chronic conditions effectively, across different cultural contexts. Previous studies have evaluated the feasibility of including telephone and Short Message Service (SMS) follow up in chronic disease self-management programs, but only for single diseases or in one specific population. Therefore, the aim of this study is to evaluate the feasibility and short-term efficacy of incorporating telephone and text messaging to support the care of patients with diabetes and cardiac disease, in Australia and in Taiwan.

**Methods/design:**

A randomised controlled trial design will be used to evaluate a self-management program for people with diabetes and cardiac disease that incorporates the use of simple remote-access communication technologies. A sample size of 180 participants from Australia and Taiwan will be recruited and randomised in a one-to-one ratio to receive either the intervention in addition to usual care (intervention) or usual care alone (control). The intervention will consist of in-hospital education as well as follow up utilising personal telephone calls and SMS reminders. Primary short term outcomes of interest include self-care behaviours and self-efficacy assessed at baseline and four weeks.

**Discussion:**

If the results of this investigation substantiate the feasibility and efficacy of the telephone and SMS intervention for promoting self management among patients with diabetes and cardiac disease in Australia and Taiwan, it will support the external validity of the intervention. It is anticipated that empirical data from this investigation will provide valuable information to inform future international collaborations, while providing a platform for further enhancements of the program, which has potential to benefit patients internationally.

**Trial registration:**

ACTRN 12611001196932.

## Background

Cardiac disease and type 2 diabetes are global health problems. In 2011, 17% of Australians (3.4 million) were reported to have cardiovascular disease [1] and these patients often suffer other comorbidities including type 2 diabetes [2]. The presence of both diabetes and a cardiac condition increases a patients’ likelihood of hospital readmission [1]. The prevalence of these conditions is predicted to increase, which will impact both health care expenditure and the health-related quality of life of people who develop these conditions [1,3,4].

With Westernisation, cardiac disease and diabetes have dramatically increased in Asian countries [5,6], with a similar prevalence of these diseases in Australia and in Taiwan [7,8]. The prevalence, mortality rate and healthcare cost of diabetes and cardiac disease have dramatically increased in Taiwan. In 2010, the prevalence of diabetes was 9.2% (2.11 million) in Taiwanese population [9]. Type 2 diabetes accounted for 11.5% of the total healthcare expenditure in Taiwan with most expenditure related to diabetic complications [10]. Cardiac disease was ranked as the second leading cause of death and diabetes was the fifth in 2010 [11].

With both countries experiencing the increasing economic and human consequences of these diseases in the context of finite healthcare and financial resources, innovative methods of health service delivery are required. A number of studies have demonstrated the effectiveness of self-management programs within the context of cardiac rehabilitation to assist patients to modify their lifestyle and achieve better health outcomes [12,13]. Self-management incorporating telephone and text-messages focussed on singular chronic diseases have also been associated with health benefits [4,14]. However, limited literature is available on self-management programs for patients with both cardiac disease and diabetes.

Some our previous work has investigated the use of home visits and telephone follow-up among cardiac patients with diabetes following an acute coronary care hospital admission to promote subsequent self management among this clinical population [15]. This pilot randomised trial with 20 participants demonstrated an increase in knowledge of cardiac and diabetes conditions among patients in the intervention group and supported the feasibility of this style of intervention [15]. The increasing popularity of Short-Message-Service (SMS) offers a useful addition to conventional telephone calls as a modality for communication between health professional and patients [16]. In a subsequent study, we investigated incorporating user-friendly and inexpensive SMS in addition to telephone calls to promote increased cardiac and diabetes condition knowledge among English-speaking Australians [17]. This cardiac-diabetes self-management program with telephone and SMS follow-up (T-CDSMP) increased knowledge of diabetes and cardiac conditions among patients in the intervention group [17].

Increasing condition knowledge is only one step toward changing self-management behaviours among patients with chronic conditions [18]. In addition to increasing knowledge, our T-CDSMP is intended to improve self-efficacy, self-management behaviours and subsequently health-related quality of life among patients with diabetes and cardiac conditions, as well as potentially reduce their risk of acute health events requiring hospital admission. It is envisaged that this T-CDSMP will not only be useful among English speaking patients, but also among patients from other cultural backgrounds where diabetes and cardiac conditions are similarly problematic.

### Aims

The primary aim of this investigation is to assess the short term effectiveness of the T-CDSMP on self-efficacy and self-care behaviour among patients with diabetes who also have cardiac disease in Australia and Taiwan. The secondary aim is to investigate the effect of the T-CDSMP on change in condition knowledge and health-related quality of life among these patients.

### Hypothesis

The hypothesis for the study is that the intervention group participants receiving the Cardiac-Diabetes Self-Management Program incorporating Telephone and Text-message reminders will increase their levels of self-management practice and self-efficacy more than the control group.

## Methods

### Design

A two group, randomised block design with blinded outcome assessment will be used to address the heterogeneity of participants from differing cultural contexts [19]. Country location (Australia or Taiwan) will be the blocking variable and will ensure equal representation of patients from each country. This trial will include a follow-up of 1 month, to evaluate the short term outcomes of self-management practice and self-efficacy, as well as condition knowledge and health-related quality of life. An overview of the study design is provided in Figure 1.

**Figure 1 F1:**
[figure not shown]
Study design: overview of data collection.

### Participants

A total of 180 patients from Australia (n=90) and Taiwan (n=90) will be recruited. Patients from each country will be randomly allocated aiming for 45 patients in control and intervention groups within each location block (Figure 1). Patients will be eligible for inclusion if they have been admitted to participating coronary care units (within Australia or Taiwan) with a diagnosis of acute coronary syndrome and a diagnosis of type 2 diabetes for more than 1 year, are aged over 18 years old, have access to a telephone / device that can receive SMS, are able to read and converse in English or Chinese, and are considered medically stable by their treating clinical team. Patients will be excluded from participation in the study if they are critically ill, unconscious, or are on respiratory ventilator support. Additionally, patients who have an inpatient stay greater than 14 days will be excluded from a per-protocol analysis (as these patients will not be at home to receive the first telephone call at the scheduled time); these patients will still be included in the intention-to-treat analysis.

Eligible patients will be approached by a trained Research Assistant (RA) to obtain their individual informed consent prior to baseline data collection. Patients will be randomised to either the control or intervention groups according to the randomisation process outlined below (Figure 1). Participants in the control group will receive the usual hospital educational program comprising routine cardiac education and referral to diabetes educator if necessary. Participants in the intervention group will receive the usual hospital educational program as well as the cardiac-diabetes self-management program incorporating telephone and text-message reminders (T-CDSMP).

### Randomisation

An independent statistician, not otherwise involved in the study, will use computerised random number generation to allocate each potential participant identification number to the intervention or control group (in a one to one ratio for both locations). The allocation sequence will only be known to this person who will conceal the allocation for each participant identification number in corresponding sequentially numbered opaque envelopes. The numbered envelopes will be stored in a locked cabinet only accessible to a randomisation gatekeeper at each of the participating locations. Participants will be assigned a participant identification number in order of recruitment. After a patient has been assigned a participant identification number and completed baseline assessments, the member of the research team responsible for coordinating the interventions at the site will receive the allocation envelope from the local randomisation gatekeeper. They will then open the envelope to reveal the group allocation for the participant. Patients will not be directly told of their group allocation (in terms of intervention or control). Instead, control group participants will continue to receive their usual care, and the intervention group participants will receive the T-CDSMP in addition to their usual care.

### Intervention

Participants who are allocated to the control group will receive the usual educational program while they are in hospital. This study involves multiple sites in different countries with differing healthcare systems; therefore, the delivery of any usual care education program will be centre-oriented to represent usual care at that facility. Data pertaining to usual care in the different centres will be collected to inform conclusions that may be drawn from location specific sub-group analyses. Patients who are allocated to the intervention group will receive the usual educational programs as well as the T-CDSMP. Research staff will be trained and supervised by the research team to deliver the intervention. The T-CDSMP, developed by the research team previously [17] is based on the self-efficacy principle of Bandura’s Social Cognitive Theory [20]. The program consists of two face-to-face sessions, one telephone call (1 week post discharge) and two SMS (1 week post telephone follow-up). The program will be delivered by a research nurse (Figure 1). Strategies used will include utilising a range of information sources (mastery, vicarious experience, verbal persuasion and self-appraisal) [20] to assist patients in developing problem-solving approaches as necessary and the basic skills of monitoring their diet, physical activity, medications and blood glucose levels. Relevant case studies using case study booklets which include real stories of common scenarios from patients in Australian and Taiwanese hospitals will be discussed and patients taught other aspects of self-care such as how to recognise signs and symptoms requiring immediate medical attention.

### Data collection

There are two primary and two secondary outcomes to be measured for this study. The two primary outcomes include self-management practice and self-efficacy. The two secondary outcomes include health-related quality of life and knowledge of the conditions. Data will be collected in two episodes: at baseline (Time 1) which is after the patients’ physical condition has stabilised and they have given their consent, but before being randomised; and one month after being discharged to home (Time 2). At baseline data collection, demographic data and outcome variables will be collected. At the second data collection, primary and secondary outcomes measures will be completed.

### Measures

Questionnaires (in English and Chinese versions) will be used for collecting data at Time 1 and Time 2. Self management behaviour will assessed using the Summary of Diabetes Self-Care Activities [21,22]. Self-efficacy will be assessed using the Diabetes Management Self-Efficacy Scale (Australian-English version and Chinese version) [23,24]. Knowledge will be examined with a knowledge of condition questionnaire [25]. Health-related quality of life will be evaluated using the brief version of the World Health Organisation Quality of Life questionnaire (WHOQoL-BREF) [26,27].

### Data analysis

Prior to the commencement of data analysis, group (intervention or control) and location (Australia or Taiwan) variables will be re-coded to a pair of numbers between one and ten to which the data analyst will be blinded. In this way, the data analyst will be blinded to the group and location data code. Data analysis will be conducted with an intention-to-treat principle. Then the analysis will be repeated (for a per-protocol analysis) excluding patients with a length of stay greater than 14 days. This planned per-protocol analysis will permit an examination of the robustness of study findings to the delayed commencement of the telephone follow-up component of the intervention among the sample (due to lengths of stay longer than two weeks). While the investigators anticipate that the intention-to-treat and per-protocol analyses will return the same pattern of findings (not many participants are likely to have an acute length of stay of greater than 14-days), the per-protocol analysis will act as a sensitivity analysis with pragmatic implications for the subsequent potential translation of the intervention into health services. If the level of effectiveness of the intervention among the study sample were influenced by the exclusion or (inclusion) of patients whose follow-up telephone call was delayed due to a longer length of stay, this would have implications for potential efforts to identify patients likely to have a longer length of stay or potential future intervention delivery modifications.

Baseline demographic information of participants in each location will be outlined for the intervention and control groups using descriptive statistics. Conventional tests of hypothesis (e.g. t-tests, Mann–Whitney U, Chi-squared) will be used where indicated to examine potential differences at baseline that may require adjustments to be made when examining the influence of group (intervention or control) and location (Australia versus Taiwan) on primary and secondary outcomes. Analysis of variance / covariance will be used to examine the main effects of group (intervention or control) and location (Australia or Taiwan) as well as potential interaction between group and location for the primary and secondary outcomes. If indicated, conventional tests of hypothesis will be used to examine differences between primary and secondary outcomes across group and location. Where assumptions for parametric analyses have not been met, data will be transformed (where possible) or non-parametric alternatives will be used to make these comparisons. Data analysis will be undertaken using the Statistical Packages for the Social Sciences (SPSS) and STATA IC with a preset alpha of 0.05.

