### Sample size

Sample size calculations were conducted based on conservative estimates to detect a between groups difference in primary outcomes at either location. For example, a location sample size of 90 has >80% power to detect a between groups mean difference of 11 points in the Summary of Diabetes Self-Care Activities outcome (scale range is 0 to 57) [21] and 10 points on the Diabetes Management Self-Efficacy Scale (scale range typically 62 to 200) [23], assuming standard deviations of 15.8 and 14.4 respectively, an alpha of 0.05, and exclusions due to long length of stay (or loss to follow up) of up to 28% of datasets at each site. Mean differences (and standard deviations) of this magnitude, and this potential attrition rate are more conservative than a prior intervention trial using these same outcome measures (but evaluating a clinic only based intervention) and our own pilot investigations [15,28]. Given the repeated measures nature of the data, and dual locations, this investigation will therefore have greater than 90% power to detect simple main effects of intervention (versus control) for the entire sample, and differences between location blocks (90 participants in each location).

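### Adjustment of the randomised comparison is tied to baseline significance tests, and the Time 1 outcome score is not fixed as a covariate

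*Protocol article*

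**What the plan says.** In the protocol article, Data analysis first promises descriptive baseline statistics by arm within location. It then says: "Conventional tests of hypothesis (e.g. t-tests, Mann–Whitney U, Chi-squared) will be used where indicated". The purpose given for these tests is "to examine potential differences at baseline that may require adjustments to be made when examining the influence of group", and likewise that of location, on the primary and secondary outcomes. The next sentence gives the model: "Analysis of variance / covariance will be used to examine the main effects of group (intervention or control) and location (Australia or Taiwan"), together with their interaction. No covariate and no time factor is named. The significance level is given as "with a preset alpha of 0.05".

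Three other places bear on this:

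- Data collection: "At baseline data collection, demographic data and outcome variables will be collected". This happens before randomisation. There is one later measurement, a month after discharge (Time 2).
- Hypothesis: intervention participants "will increase their levels of self-management practice and self-efficacy more than the control group".
- Sample size: "Given the repeated measures nature of the data, and dual locations, this investigation will therefore have greater than 90% power" for the whole-sample effect. No correlation between the two time points is given.

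**The concern.** Allocation is by a concealed computer-generated sequence, so a baseline difference between arms arises by chance. Testing it asks a question whose answer is already known. Whether adjustment is worthwhile depends on how strongly the covariate predicts the outcome, and the Time 1 score of the same scale is the natural candidate.

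The text ties adjustment to the result of such tests and gives no other basis for it. The model would then be settled only after baseline results are seen, and the measured Time 1 score would usually be unused. Two things are at stake: precision of the effect estimate, and correction of chance imbalances that fall short of significance. Precision matters most within a location, because the sample size is built on each location having more than 80% power.

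**Working it through.** **Inputs from the article.** 45 per arm per location (Participants). Under Sample size: loss or exclusion up to 28%; 11 points with SD 15.8 on the Summary of Diabetes Self-Care Activities (SDSCA); 10 points with SD 14.4 on the Diabetes Management Self-Efficacy Scale (DMSES); alpha 0.05.

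**Assumptions.** Two-sided test; the same SD at both time points; baseline/follow-up correlation r of 0.3, 0.5 or 0.7, since the article gives none.

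**1. The plan's own power.** After 28% loss, n per arm = 45 × 0.72 = 32.4. Power ≈ Φ(δ/SE − 1.96), with SE = SD × √(2/n).

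- SDSCA: SE = 15.8 × √(2/32.4) = 3.93; 11/3.93 = 2.80; power 80.0%.
- DMSES: SE = 14.4 × √(2/32.4) = 3.58; 10/3.58 = 2.80; power 79.8%.
- By the noncentral t: 78.8% and 78.6%.
- Both locations pooled, 64.8 per arm: SDSCA SE = 15.8 × √(2/64.8) = 2.78; power 97.7%, and the same for DMSES.

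The per-location figure is reproduced to within 2 points, with no margin. The whole-sample claim of more than 90% holds without any use of Time 1 scores.

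**2. How often a test gate would admit the Time 1 score.** Under randomisation, a between-arm test at 0.05 is significant with probability 0.05. Simulation gave about 5%. The score would be omitted in the other 95% or so.

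**3. What routine adjustment gives.** SE becomes SE × √(1 − r²). For SDSCA at 32 per arm, the unadjusted SE is 15.8 × √(2/32) = 3.95 and power is 79.5%.

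| r | adjusted SE | power by formula |
|---|---|---|
| 0.3 | 3.95 × √0.91 = 3.77 | 83.1% |
| 0.5 | 3.95 × √0.75 = 3.42 | 89.5% |
| 0.7 | 3.95 × √0.51 = 2.82 | 97.4% |

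**4. Test gate against routine adjustment.** Simulation with 20,000 runs per setting, one location, 32 per arm, SDSCA, true effect 11; type I error from runs with no effect.

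| r | SD of estimate, gate / always | power, gate / always | type I error, gate |
|---|---|---|---|
| 0.3 | 3.92 / 3.81 | 78.8% / 81.5% | 4.6% |
| 0.5 | 3.78 / 3.43 | 79.6% / 88.5% | 4.3% |
| 0.7 | 3.69 / 2.85 | 80.3% / 96.8% | 3.7% |

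A separate simulation of the same setting gave 79% / 78% / 80% for the gate and 82% / 87% / 97% for routine adjustment. The mean estimate under the gate was 11.0, so there is no bias averaged over randomisations.

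**5. Imbalances left uncorrected.** In about 27% of simulated trials the baseline imbalance was non-significant but had |t| > 1. In these the unadjusted SDSCA estimate moved, on average, about 1.6, 2.7 and 3.8 points in the direction of the imbalance for r = 0.3, 0.5 and 0.7. At the edge of significance the imbalance is about 1.96 × 3.95 = 7.74 points, and the expected shift r × 7.74 is 2.3, 3.9 and 5.4 points, against a target of 11.

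**The case against.** A reader might infer that the plan leaves Time 1 scores out of most analyses. The article does not say so. Its wording is permissive: tests are used where indicated, and differences may call for adjustment. It never says that a non-significant test bars a covariate. The sentence before the tests concerns demographics, so they may be aimed mainly there. The mention of covariance, the repeated-measures remark and a hypothesis about increase all suggest that Time 1 scores could enter anyway. The 5% figure is therefore conditional on the tests being the only gate and being applied to the outcome scores.

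A reader might also infer that the trial is biased or underpowered. Neither follows. The estimate is unbiased over randomisations, type I error falls slightly below nominal, and pooled power is about 97.7% at the full 28% loss. The shifts in step 5 describe particular trials with chance imbalance, as with any unadjusted comparison of randomised arms.

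Nor is every baseline difference chance: the same sentence covers location, which is a blocking variable and not randomised, so country differences may be real.

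Finally, a journal article may leave its covariate list to a fuller document. That is fair, and the absence of such a list alone would not be a finding. What stands is the rule that the article does state, which a fuller analysis plan following it would inherit. Masking the analyst to group and location codes does not fix the model.

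**Conclusion.** The point holds in a limited form. The article links adjustment of the randomised comparison to baseline significance tests, does not fix the Time 1 score as a covariate, and does not connect its model to the repeated-measures statement used for power.

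If the tests are the gate, the cost at one location with 32 per arm is power of about 78 to 80% where about 82%, 87 to 88% and 97% was available at r = 0.3, 0.5 and 0.7. The gain is small at 0.3 and large at 0.7, and the article does not say which applies. This is precision forgone, not loss of validity, and it overturns neither stated power figure. It is still worth correcting, because per-location power has no margin above 80% and the better method uses data already being collected.

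**What to change.** In Data analysis:

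- Do not use between-arm baseline tests to decide adjustment. Describe baseline by arm and location. Country differences may still be examined, since location is not randomised.
- Prespecify, for each primary and secondary outcome, an analysis of covariance of the Time 2 score on group, location, the planned group-by-location interaction and the Time 1 score of the same outcome, fitted whatever imbalance is observed.
- Reconcile this with Sample size: say that the repeated-measures remark refers to this use of the Time 1 score, and state the correlation assumed, or drop the remark.

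The cost is a wording change and one extra parameter per model. No new data are needed and no planned analysis of group, location or their interaction is lost.

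### Hypothesis, analysis and power text do not fix one treatment test: baseline adjustment is left to baseline tests, although the power statement counts on repeated measures

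*Protocol article*

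**What the plan says.** All statements are in the protocol article.

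- **Hypothesis:** the intervention group "will increase their levels of self-management practice and self-efficacy more than the control group". This is a comparison of change from baseline.
- **Data collection:** both primary outcomes are measured twice, before randomisation (Time 1) and one month after discharge (Time 2).
- **Data analysis:** "Analysis of variance / covariance will be used to examine the main effects of group (intervention or control) and location (Australia or Taiwan", together with the group by location interaction, "with a preset alpha of 0.05". The section does not say whether the analysed value is the Time 2 score, the change, or both times, and it lists no time factor. Hypothesis tests at baseline are to show whether adjustment may be needed.
- **Sample size, per location:** "a location sample size of 90 has >80% power to detect a between groups mean difference of 11 points" on the self-care scale; the matching difference for self-efficacy is "10 points on the Diabetes Management Self-Efficacy Scale". The SDs are put at 15.8 for self-care and 14.4 for self-efficacy, with alpha at 0.05. The calculation allows for "exclusions due to long length of stay (or loss to follow up) of up to 28% of datasets at each site".
- **Sample size, whole sample:** power above 90% for the effect of the intervention, introduced by "Given the repeated measures nature of the data, and dual locations". No correlation between the two times is given.

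**The concern.** The hypothesis needs the baseline score, and the power paragraph takes credit for having it. The analysis section does not commit to using it. Under the stated rule, the baseline score becomes a covariate only if a baseline test suggests an imbalance. In a randomised trial such a test is a poor guide. The value of adjusting for the baseline score comes from its correlation with the outcome, and that value is there whether or not the arms happen to differ.

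Two things are at stake. First, precision: if no imbalance is found, the baseline score may be left out and the gain cited for power is lost. Second, definiteness: an analysis of Time 2 scores, an analysis of change, a baseline-adjusted ANCOVA and a two-time repeated-measures model all fit some part of the text. They have different power, and the choice among them could be made after the data are seen.

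**Working it through.** **Inputs from the Sample size section.** Difference δ = 11 and SD σ = 15.8 (self-care); δ = 10 and σ = 14.4 (self-efficacy); alpha 0.05; loss up to 28%. Allocation is 1:1 with 45 per arm per location (Participants).

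**Assumptions of this check.** The test is two-sided (the article does not say), the SD is that of a score at one time and equal at both times, and the correlation r between Time 1 and Time 2 is 0.3 to 0.7 (not in the article).

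**Numbers analysed.** Per location: 90 × 0.72 = 64.8, or 32.4 per arm. Whole sample: 180 × 0.72 = 129.6, or about 64 per arm.

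**Formula.** Power = Φ[(effect / SD) × √(n/2) − 1.96], with n per arm.

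**Step 1: the plan's own per-location figure.** Self-care: 11/15.8 = 0.696; 0.696 × √16.2 = 2.80; 2.80 − 1.96 = 0.84; power 80.0%. Self-efficacy: 10/14.4 = 0.694; power 79.8%. With the noncentral t the results are 78.8% and 78.6%. The plan's figure is reproduced to within 2 points, though its 'greater than' is borderline.

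**Step 2: the whole sample with Time 2 scores only.** 0.696 × √32 = 3.94; 3.94 − 1.96 = 1.98; power 97.6% (t: 97.4%). Power above 90% is therefore met without any gain from repeated measures.

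**Step 3: the analyses the text leaves open, self-care scale, 64 per arm.** Self-efficacy is within 0.3 points.

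| Treatment test | Effect | SD | r = 0.3 | r = 0.5 | r = 0.7 |
|---|---|---|---|---|---|
| Time 2 score only | 11 | 15.8 | 97.6% | 97.6% | 97.6% |
| Change score, or group × time | 11 | 15.8 × √(2(1−r)) | 91.4% | 97.6% | 99.9% |
| ANCOVA on Time 1 score | 11 | 15.8 × √(1−r²) | 98.5% | 99.5% | >99.9% |
| Group term averaged over both times | 5.5 | 15.8 × √((1+r)/2) | 68.5% | 62.3% | 57.0% |

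In the last row the Time 1 difference has expectation zero, because Time 1 precedes randomisation, so the average is (0 + 11)/2 = 5.5. At r = 0.5 the SD is 15.8 × √0.75 = 13.7; 5.5/13.7 = 0.402; 0.402 × √32 = 2.27; 2.27 − 1.96 = 0.31; power 62.3%. With the t distribution this row runs from about 68% to 56%, and simulation agrees (68.0%, 61.9%, 56.5%).

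**Step 4: what always adjusting gains within a location, 32 per arm.** Time 2 only: 0.696 × √16 = 2.78; 2.78 − 1.96 = 0.82; power 79.5%. ANCOVA at r = 0.5: 11/13.7 = 0.804; 0.804 × 4 = 3.22; 3.22 − 1.96 = 1.26; power 89.5%. At r = 0.3 it is 83.1%, and at r = 0.7 it is 97.4%.

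**The case against.** The strongest reply is that the article plans nothing unsound. The listed terms form a two-by-two layout with one value per patient. The word covariance, next to the mention of adjustment, fits an ANCOVA with the baseline score as covariate. The remark on repeated measures may only describe data collected twice. An article also condenses a fuller protocol and analysis plan, to which model details commonly belong.

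Much of this stands. In an analysis of Time 2 scores, of change, or by ANCOVA, the group main effect is the full treatment effect. The claim of more than 90% power holds for Time 2 scores and for ANCOVA, and for change scores from a correlation of about 0.3.

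A reader might go further and infer that the planned main effect averages baseline and follow-up, halves the effect and does not test the hypothesis. The article does not support this. Nowhere does it say that baseline will be a level of the outcome in a repeated-measures ANOVA, and the absence of a time factor speaks against it. Even in that model the averaged term would be zero under no treatment effect: a valid test, but a diluted one.

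The reply does not cover what the article does state: a rule that makes adjustment depend on baseline tests, beside a power argument that relies on using both measurements. That is a mismatch in the text, not a detail left out.

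**Conclusion.** The point holds as an inconsistency with a modest cost. The hypothesis is about a greater increase, the analysis section does not commit to the baseline score, and the power section counts on it.

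The whole-sample power claim survives, at about 97% with Time 2 scores alone. It would fail, at about 56% to 68% for assumed correlations of 0.7 to 0.3, only if both times entered a repeated-measures ANOVA and the group main effect were read as the treatment test, which the text does not say.

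The realistic loss is precision. It matters most within a location, where the stated power has no margin: about 79.5% without the baseline score against 83% to 97% with it, for correlations of 0.3 to 0.7. These figures rest on the article's differences, SDs and 28% loss, a two-sided test, equal SDs at both times, and correlations that the article does not give.

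**What to change.** 1. In Data analysis, state for each primary outcome that the treatment test is the group coefficient in an ANCOVA of the Time 2 score, always adjusted for the Time 1 score and location. Location is the randomisation block, so it belongs in the model in any case.
2. Add group × location to that model as a second step, for the interaction question only, so that the group coefficient in the first step keeps its meaning across both countries.
3. Delete the dependence of adjustment on baseline tests. Baseline tables can remain descriptive.
4. If a repeated-measures model is kept instead, state that group × time is the treatment test.
5. In Sample size, refer the power statement to the chosen term and give the assumed correlation with its source, or base the statement on Time 2 scores alone and remove the reference to repeated measures.

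The cost is a few sentences. Both scores are already collected, and neither the sample size nor the visits change.
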